**Consent**

A member of the research team (either research assistant [RA] or chief investigator [CI]) will facilitate the telephone interview (hereafter referred to as researcher). They will have received training in good research governance and Good Clinical Practice (GCP) no more than two years prior to the interview.

On the day of the interview, but prior to commencement, the researcher facilitating the interview will explain the aim and demands of the telephone call and answer the participant’s questions. The researcher will then explain that the telephone call will be recorded, and invite the participant to agree to the audio recording. If the participant agrees, the researcher will press record. If the participant declines, the researcher will end the interview and provide a full explanation as to why.

Next, the researcher will invite the participant to give verbal informed consent. Each consent statement of the consent form will be read verbatim by the researcher, to which the participant will be invited to verbally agree by replying ‘*yes*’. These consent statements will include an explanation that their data will be held confidentially under the Data Protection Act 2018 and that they may withdraw from the interview at any time without implications for their standard health care, without affecting their legal rights, and with no obligation to answer further questions or state the reason for withdrawal. The letter invitation and PIS will also explain the right to withdraw. Each statement numbered 1 to 7 are required statements (i.e. non-optional) and failure to provide informed consent on one or more will terminate the participant’s involvement in the study.

The researcher will initial each point to indicate verbal consent was provided. Since the verbal consent will be audio-recorded it will also be transcribed verbatim. The research team at the sponsor site will securely retain both original copies of the researcher-initialled and verbally transcribed consent transcript. The RA will post copies of the researcher-initialled consent form to the participant.

The PIS contains the Oxford University Hospitals (OUH) Patient Advice and Liaison Service (PALS) contact details should the participant wish to discuss the interview with an independent party outside of the central research team.

**Interview**

**Telephone Call (30 minutes)**

The researcher will telephone call participants on the arranged date and time. Telephone calls will be made in a pre-booked, quiet room at the University of Oxford. They will be audio-recorded and last approximately 30 minutes.

First, participants will be required to confirm their name. Next, the researcher will remind participants of the PC-SHOP intervention study. The researcher will describe the overall structure of the telephone call and provide an opportunity for the participant to ask questions.

The researcher will then explain that the telephone call will need to be recorded, invite the participant to provide consent for audio recording and then press record accordingly. The participant will be invited to provide verbal informed consent. The researcher will read a series of seven required statements pertaining to voluntary participation, data collection and management, and anonymisation and confidentiality. The participant will be required to reply ‘*yes*’ if they consent. If the participant declines consent to one or more statements, they will be thanked for their time and receive and the telephone call will end. The researcher will explain why. These participants will still receive the store card reimbursement.

Consented participants will be asked around 10 questions pertaining to the following themes: (1) understanding of saturated fat and the effects on health (2) the intervention components and impact on behaviour, and (3) support from healthcare professionals to improve health. For example, “*what did you think about healthier swaps suggested?*” (Question 7). All members of the PC-SHOP research team have developed and piloted the topic guide. In line with qualitative research methods, minor edits to the topic guide may be made during the data analysis if unexpected themes begin to emerge.

At the end of the interview, the researcher will provide participants with the opportunity to add any other thoughts. They will remind participants to expect a letter in the post with the researcher-initialised consent form and a £20 store card as reimbursement for their time. The researcher will then stop the audio recording.

**Audio Transfer to Secure Storage**

The Information Asset Registrar form defines this study’s audio recordings as an asset. Hence, all audio recordings will be uploaded to the University of Oxford’s electronic secure storage facility accessible only by the research study team. These audio recordings will be transformed into an encrypted zip file using 7 Zip. The research team will then store recorders (as well as all study data documents, including the consent form) securely in a locked cabinet, in a locked room within a restricted access building with keypad access control system.

**Audio Transcription**

The encrypted zip files will be sent for transcription via OxFile to approved external transcribers, with confidentiality and conduct contracts in place with the University of Oxford. The process for transferring the zip files will be performed according to local Information Governance policy; in password-protected files, with the agreed password transferred via a separate form of contact i.e. different email address or telephone number. The external transcriber shall transfer transcriptions back to the researcher via OxFile. The original audio files will be deleted from the recorder once the transcripts have been checked for fidelity and any queries resolved. Once transcripts have been checked, the study team will de-identify them (e.g. deleting any references to identifiable information such as names) before they are stored. Transcriptions will be stored anomymously in the electronic secure storage facility, backed up, and archived using the University of Oxford Hierarchical File Server (HFS) Backup service.

**Analysis of the qualitative study**

Verbatim transcriptions will be analysed using the NVivo 11 software programme^4^. A thematic analysis approach will draw out themes, categories and nodes from the data pertaining to the (i) knowledge, (ii) perceived barriers and facilitators, (iii) contextual influences, and (iii) value of the healthcare advice provided. One researcher will deductively code the transcript data against an initial thematic framework using the Framework Method^5^, which comprises five steps: (i) familiarisation, (ii) developing a thematic framework, indexing, charting, mapping and interpretation.

A second researcher will check a sub-sample of 10 percent for validity and inter-rater reliability. In instances where it is unclear how to code themes against the initial framework, discussion with a third reviewer will reach consensus on whether to form a new theme or whether to expand an existing theme.

Thematic coding will begin once data collection starts in a process of iterative data gathering and analysis i.e. a zigzag approach. Early analysis will inform further data gathering. For this reason, the topic guide will be subject to ongoing review and edits if unexpected themes begin to emerge. Findings will be synthesised narratively.

# INTERVENTIONS

The two active interventions will incorporate strategies which use the Behaviour Change Wheel COM-B model as a theoretical framework to guide the choice of behavioural strategies^13 17^. Briefly, the proposed interventions aim to allow participants to develop and sustain the capability, opportunity and motivation to make changes to diet^13^. Psychological capability will be enhanced by educating participants on SFA and health risks as well as information on the most appropriate swaps to decrease their SFA intake. Opportunity will be supported by the shopping report which will highlight the top 3 individual sources of SFA and proposed swaps to those, therefore making healthier choices easier to spot by participants. Motivation will be promoted by the shopping report by allowing participants to track and monitor their progress over time, as well as by the health professional advice which will provide further motivation to attempt the change and facilitate understanding of the value of these changes on health.

Participants will be randomised to one of the three conditions explained below. Participants randomised to receive intervention 1 and 2 which involves a brief advice session, will be asked to consent to have the session audio-recorded to allow for fidelity testing. The purpose of fidelity testing is to determine:

- If the brief advice session in being delivered according to the intended protocol and behavioural theoretical models.

- If number frequency, length and content of the sessions are similar across all participants within each group.

- Compare and identify successful and unsuccessful aspects of the interventions.

## Intervention 1: Brief advice session

This intervention will be a single one-to-one appointment with the health professional (HP) in which they will receive advice on the importance of dietary change and motivation to reduce SFA based on the British Heart Foundation “*Cut the Saturated Fat*” chart^18 19^, which will be provided as printed educational material.

This session is aimed to inform participants about the benefits of saturated fat reduction and encourage them to attempt it. Dietary advice will be particularly focused on explaining the different sources of fat and the most appropriate changes proposed in the BHF guidance to decrease SFA, primarily by substitution with lower SFA options (e.g. change from regular beef to lean beef); or with mono- and polyunsaturated fat sources (e.g. change from butter to low-fat vegetable spread).

Health professionals will be trained to deliver this session face-to-face during approximately 10min. The structure of the session will be standardised so that it will follow 3 major discussion points. The HP will start by discussing cardiovascular risk with the participant and will provide the participant with the results of the blood tests. The HP will then highlight that diet is a very important modifiable risk factor which can potentially help them decrease this risk by lowering their blood lipids. The second point of discussion will focus on the major sources of SFA in different foods. The HP will carefully explain the educational materials with special emphasis on the major sources of SFA in the UK (dairy, meat and cakes/biscuits). The session will end with a few minutes for questions and final remarks in which the participant can ask any questions in regards to the information provided and the HP will finish the session by emphasising that the proposed changes can achieve very good results in a short time period.

## Intervention 2: Brief advice session and shopping report

In addition to the brief advice session detailed above, participants in this intervention arm will receive a personalised report with the nutritional composition of foods and beverages purchased from Tesco over the previous 3 months (baseline) and subsequent months (monthly over the 3 months of follow up). This report will include information on total saturated fat (g) and the major food contributors to SFA. Participants will receive monthly reports to allow them to chart their progress in reducing SFA in their grocery purchases. This information will be accompanied by a list with suggestions for one-for-one swaps for foods high in SFA for lower SFA foods to support dietary change.

## Control group

Participants in the control group (usual care) will be recruited into the study and will be informed of their blood tests by the study team. They will be seen again at 3 months for collecting outcome measures.

Upon completion of the study, all participants including those in the control group will receive a final report with the nutritional information of their purchases over the 3 months during which they were enrolled in the intervention. The control group will also be sent the BHF booklet.

# SAFETY REPORTING

This intervention will only provide standard dietary advice which is consistent with recommendations from scientific advisory committees in the UK and internationally and there is no known risk from eating food lower in SFA. Due to this, we will only report serious adverse events that the PI believes are related to the trial, which will be considered unexpected.

## Definition of Serious Adverse Events

A serious adverse event (SAE) is any untoward medical occurrence that:

- results in death
- is life-threatening
- requires inpatient hospitalisation or prolongation of existing hospitalisation
- results in persistent or significant disability/incapacity
- consists of a congenital anomaly or birth defect.

Other ‘important medical events’ may also be considered serious if they jeopardise the participant or require an intervention to prevent one of the above consequences.

NOTE: The term "life-threatening" in the definition of "serious" refers to an event in which the participant was at risk of death at the time of the event; it does not refer to an event which hypothetically might have caused death if it were more severe.

## Reporting Procedures for Serious Adverse Events

The duration of the SAE recording period lasts from enrolment on to the study to the end of the termination of their programme. All SAEs, deemed related by the PI, will be recorded at the time the central research team become aware of the incident. This may occur at study assessment visits, via notification from the clinical team or when the central research team contact participants by telephone or email.

The following information will be recorded for each SAE:

- Description,
- Date of onset and end date,
- Severity,
- Action taken,
- Follow-up information should be provided if deemed clinically necessary.

If there are any unexpected related SAEs, these will be reported to the Research Ethics Committee in accordance with HRA process.

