# STUDY DESIGN

For this study, an individually randomised, 3 arm, parallel group design will be employed.

Due to the nature of the intervention, it will not be possible to blind participants, clinicians or some of the study team to the treatment allocation once the intervention commences, but they will be blind at the point of randomisation.

Patients’ participation in the study will last 3 months from randomisation to final follow-up. Details of the sequence and duration of all study periods are included in the appendix together with the flowchart of the project.

Briefly, participating practices will search their records for eligible participants who meet the essential inclusion criteria: a) adults and b) with a record of high LDL cholesterol over the last 24 months. Invitation letters will be sent with the team contact information and study details, including other inclusion criteria a) participant is primarily responsible for the household grocery shopping and b) participant shops at Tesco at least once a week using a Tesco storecard.

Interested participants who believe they meet the criteria will be invited to contact the central research team via email who will assess them further over the phone to check eligibility. Those who meet all the eligibility criteria will be booked for the first baseline visit. Previous to the first baseline visit, participants will be asked to provide the first 24h dietary recall (using a validated online questionnaire performed on a computer). This data will be stored independently of the study team before full consent is obtained.

At the baseline visit participants will provide full informed consent and a blood sample by fingerprick will be taken by the central research team. Additionally, the central research team will collect other baseline measures, including a second 24h dietary recall, weight and height, blood pressure and their Tesco’s clubcard number. Once the blood tests confirm that each participant has raised LDL cholesterol and that they have completed two dietary recalls, the central research team will randomise them to one of the three interventions. Those allocated to brief advice session or brief advice session with purchasing report will be booked for an appointment with the health professional at their practice within a week after the baseline visit preferably. Those allocated to the control arm will receive usual care, which consists of providing their blood results.

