## Three-month follow up assessment

A follow up and final visit will be completed at least 3 months and no more than 4 months after randomisation to assess the main study outcomes. Therefore, all the measures collected as part of the baseline visit will be repeated following the same procedures and conditions as described above.

The central research team will collect the following measurements at the practice:

- Fasting fingerprick blood sample, to be analysed for blood lipids (LDL, HDL, total cholesterol, non-HDL cholesterol, total cholesterol/HDL ratio and triglycerides) using a portable lipid testing system, will be taken by the central research team,
- Any changes in knowledge with regards to diet and SFA as well as intervention acceptability collected by questionnaire,
- Changes to relevant medical history and all concomitant medication,
- Dietary intake will be collected using a validated web-based 24-h recall dietary questionnaire, which will be completed twice at follow up, once prior to the follow up visit, and a second one at the in-person visit. Participants will be given the opportunity to come to the practice to complete their dietary recall if they are unable to access a computer and internet at home,
- Seated systolic and diastolic blood pressure,
- Weight.

- Changes to drug treatments during the course of the study: the clinical team in the practice will decide which, if any medications need to be adjusted as a result of changes in health status during the course of the study. However, we will ask participants and clinicians to refrain from altering any lipid-lowering medication during the 3-months of follow-up unless strictly necessary.

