## Trial Steering Committee / Data Monitoring Committee

Due to the low risk nature of the PC-SHOP trial and that it is an open label trial, the Trial Management Group will act as the Trial Steering and Data Monitoring Committee to provide oversight of all matters relating to participant safety and data quality.

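### Section 10.2 makes the PI's judgement of relatedness a condition for recording an SAE, so events judged unrelated leave no SAE record to review or to tabulate by arm

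*Protocol*

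**What the plan says.** The opening of section 10 (Safety Reporting) argues that the intervention is standard dietary advice and that "there is no known risk from eating food lower in SFA". From this it concludes that "we will only report serious adverse events that the PI believes are related to the trial, which will be considered unexpected".

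Section 10.2 then sets the recording rule: "All SAEs, deemed related by the PI, will be recorded at the time the central research team become aware of the incident". The items to be kept for each SAE are a description, start and end dates, severity, the action taken and, where clinically needed, follow-up. Relatedness, the person who judged it, the seriousness criterion met and the trial arm are not among them. A separate sentence in 10.2 sends unexpected related SAEs to the Research Ethics Committee.

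On blinding, section 6 says that "it will not be possible to blind participants, clinicians or some of the study team to the treatment allocation once the intervention commences". Section 13.3 gives as its reason for having no separate committee: "Due to the low risk nature of the PC-SHOP trial and that it is an open label trial". The Trial Management Group therefore acts as steering and data monitoring committee, "to provide oversight of all matters relating to participant safety and data quality". Section 13.1 lists its members, who include the Chief Investigator and one independent statistician.

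**The concern.** Restricting expedited reports to related, unexpected events is a proportionate choice for a low-risk dietary trial and is not at issue. Section 10.2 goes a step further and applies the same filter to recording. A causality judgement is normally a field completed after an event has been logged. Here it is the condition for logging the event.

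Two things follow. First, an SAE judged unrelated leaves no SAE record, so the body charged with safety oversight cannot readily review that judgement. Second, what is recorded depends on a subjective judgement made in an open-label trial. If that judgement tends to differ by arm, the recorded events will differ by arm even where the underlying events do not. An analysis plan cannot repair this later, because events that were never recorded cannot be analysed.

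**Working it through.** The protocol states no figure on this point, so the check is mainly of the text, with arithmetic for scale only.

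**1. Is recording really filtered?** The commas in the section 10.2 sentence could be read as describing all SAEs loosely. Two things favour the restrictive reading. The opening of section 10 says that "we will only report serious adverse events that the PI believes are related to the trial", and the list of recorded items has no causality field, which would be needed if unrelated events were also entered. The onward-reporting filter has its own sentence in 10.2, so the filter on recording is an additional one.

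**2. Who judges, and with what knowledge?** The PI judges. The abbreviation is not defined in section 3, and the protocol elsewhere refers to the Chief Investigator. The PI's blinding status is never stated. The trial is called open label, and no blinded or second SAE assessor is specified.

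**3. Can the filter act unequally?** Under section 9.3, controls are told their blood results and seen again at 3 months. The report and booklet reach them only on completion. Apart from study procedures such as the fingerprick sample, there is little to which a control SAE could be attributed.

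An illustration of direction, with every rate assumed: let the true SAE risk be 5% in all arms, and let 20% of events in the active arms and 0% in control be called related.

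- Active arms (n = 48 + 48 = 96): 96 × 0.05 = 4.8 events, of which 4.8 × 0.20 = 0.96 recorded.
- Control (n = 16): 16 × 0.05 = 0.8 events, of which 0.8 × 0 = 0 recorded.

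Equal risk then appears as a difference produced by the filter. With 20% called related in every arm, control would have 0.8 × 0.20 = 0.16 recorded, and the two recorded rates would both be 1%.

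**4. How many records would full recording add?** Arm sizes are from section 11.2. The protocol gives no SAE rate, so 1–3% over follow-up is an assumption. Expected count = n × p; chance of at least one event = 1 − (1 − p)^112.

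| Assumed risk p | Control (16) | Each active arm (48) | Total (112) | At least one in trial |
|---|---|---|---|---|
| 1% | 0.16 | 0.48 | 1.12 | 68% |
| 2% | 0.32 | 0.96 | 2.24 | 90% |
| 3% | 0.48 | 1.44 | 3.36 | 97% |

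Full recording therefore means about one to three entries.

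**5. Do other records fill the gap?** Section 8.5.1 collects "Changes to relevant medical history and all concomitant medication" in all arms at 3 months. Section 8.10 puts reasons for withdrawal in the CRF, and section 14.5 seeks consent for access to medical records. These could reveal some events. None is an SAE log. The 3-month update also depends on attendance, and section 11.2 assumes about 10% attrition.

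**The case against.** The strongest case against is that this is a deliberate, reasoned choice. Section 10 gives its rationale, sections 10 and 10.2 agree with each other, and the intervention is brief dietary advice over 3 months. No objective or outcome concerns SAE frequency, so there is no planned safety result for the filter to bias. With fewer than 0.5 events expected in control at the assumed rates, even a complete table would say little about differences between arms. All of this stands, and it limits the weight of the point. It does not explain why recording, rather than onward reporting alone, has to be filtered.

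Some stronger readings are tempting but are not supported by the documents:

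- A reader might infer that an unblinded PI makes the judgement. That is plausible in an open-label trial, but section 6 says only that some of the study team cannot be blinded.
- A reader might infer that the recorded count will be near zero whatever happens. That presumes the PI would reject almost every event; an event recognised as caused by the trial would be recorded.
- A reader might infer that oversight has nothing at all to check against. The sources in sections 8.5.1, 8.10 and 14.5 allow a partial check.
- A reader might infer that full recording with no events would give firm upper limits on SAE risk. The one-sided 95% limits, 1 − 0.05^(1/48) = 6.1% and 1 − 0.05^(1/16) = 17.1%, require complete ascertainment. Recording that relies on the team becoming aware of events, with 10% attrition, does not provide it.
- A reader might infer that biased safety data would be carried into a later trial. The definitive trial in section 4 is conditional on promising results and is described in terms of LDL cholesterol; nothing is said about carrying safety data forward.

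**Conclusion.** The point holds in a limited form. Section 10.2, supported by section 10, makes relatedness the condition for recording an SAE. Events judged unrelated leave no SAE record, and because controls receive no study intervention during follow-up, the filter can act unequally by arm. This sits poorly with the oversight role given to the Trial Management Group in section 13.3, which cannot readily review those judgements or see all SAEs by arm.

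The practical weight is modest. Efficacy conclusions and the sample size are untouched, and a full SAE table would be descriptive only. The conclusion rests on the restrictive reading of the 10.2 sentence and on the absence of any blinded or second assessor in the protocol. The size of the recording burden rests on an assumed SAE risk, while the unequal-filter figures illustrate direction and are not an estimate.

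**What to change.** In section 10.2, require every SAE that the team becomes aware of to be recorded, in all arms, with trial arm, seriousness criterion, relatedness judgement and assessor added to the listed items. State that all SAEs will be tabulated descriptively by arm and made available to the Trial Management Group. Align the opening of section 10 so that its restriction clearly concerns onward reporting. Leave reporting to the ethics committee limited to related and unexpected events, as now.

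The cost is a wording change, a few added CRF fields and about 1 to 3 extra entries at the assumed risk of 1–3%. No extra visits or staff are needed, and the 3-month medical history update already gives the team an occasion to learn of events.
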